## Abstract

**Background:**

School dropout is considered a serious problem in high schools in Norway. Despite studies which emphasize the importance of mental health as a unique risk factor for dropout, interventions have only taken this into account to a limited extent. Depression is one of the most prevalent mental health issues. Here we report the study protocol of a cluster randomized controlled trial of a group-CBT intervention, “*Adolescent Coping with Depression Course*” (ACDC) for depressed adolescents in upper secondary school.

**Method:**

The aim of this study is to investigate the extent to which ACDC can reduce depressive symptoms, prevent dropout and improve academic and social functioning among adolescents in upper secondary school. This study investigates the effectiveness of ACDC through a cluster randomized trial, in which course leaders are randomized to experimental or control conditions where the control groups receive usual care.

**Discussion:**

The intervention is expected to reduce depressive symptoms among adolescents. The study will further investigate whether the intervention can prevent dropout and improve academic and social functioning among adolescents in upper secondary school.

**Trial registration:**

ISRCTN registry ISRCTN19700389. Registered 6 October 2015.

**Electronic supplementary material:**

The online version of this article (doi:10.1186/s12888-016-0954-y) contains supplementary material, which is available to authorized users.

## Background

Dropout is considered a serious problem in upper secondary schools in Norway [1]. Despite international studies which emphasize the importance of mental health as a reason for school dropout [2, 3] Norwegian interventions have only taken this into account to a limited extent [4]. In general fewer than 20 % of adolescents who are in need of help for mental health problems have been in touch with health services for this reason [5]. On the basis of this, we assume that a relatively large group of students that we meet every day in our schools in Norway do not get proper support to cope with their school functioning. Depressive symptoms are among the most common forms of mental health problems in adolescents [6]. The overall aim of the proposed study is to investigate the effectiveness of a group-based cognitive behavioral therapy (CBT) intervention for depressed adolescents, *Adolescent Coping with Depression Course* (*ACDC*), in upper secondary school, and to see whether it has an impact on dropout rates.

### Dropout is strongly related to mental health

One third of Norwegian students drop out of upper secondary school [1] with the highest rates for vocational students [7] and immigrants [8]. The dropout rates are problematic because of the increasing need for formal education in order to get a job [4]. In Norway about one-third of those who are considered disabled on the basis of a mental illness have never received any treatment, and depression is the main reason for the disability [4, 9]. Studies suggest mental health as a unique risk factor for dropout [2, 3]. One study from the USA estimates that over half of those who drop out of secondary education have a diagnosable mental disorder [3]. In a study from one Norwegian upper secondary school, 20.8 % of the dropouts reported mental health problems as the cause [10]. In general, as many as 15–20 % of Norwegian adolescents report clinical range mental health problems [6], but only 16–17 % of those 15–20 % have consulted mental health services [5, 11]. This means that a large group of young people in need of help do not receive it, which again may cause additional challenges for schools in supporting this large group of “unhelped” students all the way from start through graduation. Finding better ways of supporting students at risk may also be beneficial for school motivation because of the relationship between academic issues and mental health [12, 13].

### Depression the most common mental health problem

According to the World Health Organization one of the most common disabling diagnoses is depression [14] with a peak age for first onset ranging from 15 to 21 years [14, 15]. In Norway this is one of the most common forms of mental health problem among children and young people [6], and the number of adolescents being disabled by depression is increasing [16]. Research findings from Norway also show more academic discrepancies and higher prevalence of mental health problems among immigrant youths, compared to their host peers throughout elementary, secondary and high school years [17]. Depression and depressive symptoms are characterized by impairments in cognitive, emotional and social functioning. Precisely these things are highly important for academic and social success. Targeting depression could thereby be highly relevant to decreasing dropout rates and increase academic motivation among students.

Depression is associated with a range of problems, like school dropout, school difficulties, health problems, increased substance abuse, suicide, as well as problems with peers and family [18–21]. Furthermore, it seems clear that the need for mental health care for young people is unmet [5]. Of more concern is that failure to seek early treatment is associated with longer disease course and more relapsing episodes [22]. Even subclinical depression among adolescents is associated with increased risk of depression and suicide attempts in adulthood [23]. In Norway, the mental health services and the municipalities have been strengthened in areas such as early identification of illness, prevention and early treatment [24]. This has been extended in recent government documents putting the focus on early intervention even higher. However, specialist mental health services still only seem to reach a minority of these adolescents [11]. Altogether, the prevalence estimates of depression as well as the public health consequences, high dropout rates and the failure to seek treatment suggest that effective interventions targeting adolescents with symptoms of depression need to be provided in places where they can be accessed – such as school.

### Schools as arenas for supportive interventions

A larger number of depressed students could probably be accessed if supportive interventions were provided closer to school. Schools are optimal places for such purposes as they provide access to all children, including those targeted for intervention, on a regular basis and over time. Immigrant students, who underuse mental health services [25] may gain particular advantage from school-based interventions. Group-based approaches could very well be implemented in relation to schools, either by the educational psychological service, school nurses or counselors/special educators at school. This could also counteract some of the unequal access to treatment related to social status. Investigations from Statistics Norway show that people with lower education receive little help from psychologists within the specialized services [26, 27].

### Group- based cognitive behavioural therapy (CBT) interventions

Some of the most effective interventions in treating depression among adolescents are based on cognitive behavioural therapy (CBT) [28]. Within CBT the main target is to change and modify maladaptive cognitions and behaviours that constitute the three core processes of depression [29]. Group-based CBT interventions for depressed adolescents have provided efficacy for adolescents with diagnosis of major depression or dysthymia [30–33] but also when used to prevent further development of subclinical depression among adolescents [34, 35].

## Methods

### Aim of the study

The aim of this study is to evaluate the *Adolescent Coping with Depression Course* (*ACDC*), a CBT program, compared to practice-as-usual control treatment in reducing depressive symptoms and preventing dropout among upper secondary school students, as well as increasing their academic and social functioning. Our main research questions are: 1) What are the effects of ACDC on depression, dropout, achievement and social functioning among students in junior high school? 2) Is immigrant status a possible moderator of the effects of ACDC?

### Design

Figure 1 presents the general design of the study, and see also Table 1. Assessments are administered at initial screening (T0), before the ACDC starts (T1), after the course finishes (T2) and 6 months (T3) and 12 months (T4) follow-ups.

**Fig. 1 Fig1:**
[figure not shown]
Overview of the study design

**Table 1 Tab1:** World Health Organization Trial Registration Data Set

Data Category	Information
Primary registry and trial identifying number	ISRCTN registry ISRCTN19700389
Date of registration in primary registry	6 October 2015
Secondary identifying numbers	Protocol/serial number: 238081
Source(s) of monetary or material support	The Norwegian Research Council
Primary sponsor	The Norwegian Research Council
Secondary sponsor(s)	The Norwegian Center for Child Behavioral Development
Contact for public queries	[name] [contact]
Contact for scientific queries	[name] [contact]
Public title	Effectiveness study of a CBT based adolescent coping with depression course
Scientific title	Effectiveness study of a CBT based adolescent coping with depression course to prevent dropout in upper secondary school
Countries of recruitment	Norway
Health condition(s) or problem(s) studied	Mild/moderate depression among adolescents
Intervention(s)	Active comparator: CBT-based group intervention, 8 consecutive weekly sessions of 120 min, two follow-up sessions conducted about 3 and 6 weeks after the last session, lasting approximately 90 min
	Placebo comparator: Usual care
Key inclusion and exclusion criteria	Cluster-randomized design where the course-leaders are recruited from the School Health Service, Public Health Nurses, the Educational and Psychological Counselling Services (PPT). They are then taught how to recruit a group of 1st or second year students from Upper Secondary School (Videregående skole). A complete assessment of possible participants (adolescents) has to be made by the course instructors before acceptance into the study.
	Inclusion criteria for adolescents:
	1. First or second year of upper secondary school (about 16–17 years old)
	2. Who have subclinical depression or mild to moderate major depressive disorder (MDD), according to the criteria of the DSM
	3. Normal intellectual functioning
	4. Normal reading abilities, and that was evaluated through the interview.
	Exclusion criteria for adolescents:
	1. Bipolar disorder
	2. Psychosis
	3. Substance-use
	4. ADHD or ADD
	5. Brain damage
	6. Danger of suicide
	7. Adolescents who are easily agitated
	8. Adolescents who lack the ability to function in a group
Study type	Single-centre cluster-randomized effectiveness trial with active control. Primary study design
	Interventional, Secondary study design
	Cluster randomised trial
Date of first enrolment	01/11/2015
Target sample size	35 clusters with 8–12 adolescents within each cluster
Recruitment status	Recruiting
Primary outcome(s)	1. Center for Epidemiological Studies Depression Scale, CES-D for adolescents, at Pre-test, T1, T2, T3, T4
	2. Dysfunctional Attitudes Scale (DAS) (short version) at Pre-test, T2, T3, T4
	3. Automatic Thoughts Questionnaire (ATQ) (short version) at Pre-test, T2, T3, T4
	4. Ruminative Response Scale (RRS) (short version) at Pre-test, T2, T3, T4
	5. Emotion regulation at Pre-test, T2, T3, T4
	6. Dropout (from school and official registries) at T1, T2, T3, T4
	7. Grades at T1, T2, T3, T4
Key secondary outcomes	1. Intentions to quit school at Pre-test, T2, T3, T4
	2. Social and Cognitive Competence at Pre-test, T2, T3, T4
	3. Life events at Pre-test, T2, T3, T4

Course leaders were recruited from the Educational Psychological Services, School mental health offices, and so on. To become certified as an ACDC course leader, one must have completed a minimum 3–year college/university education before attending the 5 day certification course. The trainers are either doctors, psychologists, nurses, educators, social workers, occupational therapists or physiotherapists. All are employed in community health, public health/public hospitals, schools or in private healthcare.

The course leaders have been randomized to experimental and control conditions by administrative personnel at the Norwegian Center for Child Behavioral Development. The control groups of adolescents will receive practice as usual, so those course leaders will be offered their training shortly after the experimental groups have finished after 14 weeks. Our design is thereby a cluster randomized trial where groups (course leaders) rather than individuals are randomized.

Participants (adolescents with depressive symptoms) are recruited by the ACDC trainers (both intervention and “active control” ones), and they are offering their own courses by placing information on schools and health centers, providing information through GPs, advertisements in local newspapers, on websites for youth, information on the local hospital’s medical meetings. Participants are recruited by either themselves take direct contact with course retainers, or they are referred by health visitors, GPs, psychiatric clinics, municipal services, school counselors, and the like. It will be established with doctor/referring in terms of differential diagnosis and considering further action after the course if necessary.

Fifteen course leaders for the intervention group received their training for a full week in October 2015, while the 15 leaders of “practice as usual” received a one-day training in how to recruit adolescents in October. Adolescents have been recruited throughout November and December 2015. Following a screening interview, baseline measures of all study measures was administered (see Table 2). The trial of the first cohort started in January 2016 and ran for 14 weeks, either by 10 sessions of the ACDC (treatment condition) or “practice as usual” for the control condition. Two weeks before the trial, the main outcome measure of depression was assessed. In addition to post-test in spring 2016, we will collect 6- and 12- month follow-ups. Personal number will be kept for five years in order to collect relevant information from public registers to further examine dropout.

**Table 2 Tab2:** Measures to be administered at each measurement occasion

Measure/Scale	References	S	T0	T1	T2	T3	T4
Beck Depression Inventory	Beck et al. 1961 [42]	X					
Demographics			X				
Center for Epidemiologic Studies Depression Scale (CES-D)	Radloff, 1977 [44]		X	X	X	X	X
Dysfunctional Attitudes Scale (DAS)	De Graaf et al., 2009 [53]		X		X	X	X
Ruminative Response Scale (RRS)	Nolen-Hoeksema & Morrow, 1991; Treynor et al., 2003 [55, 56]		X		X	X	X
Automatic Thoughts Questionnaire (ATQ)	Hollon & Kendall, 1980; Netemeyer et al. 2002 [51, 52]		X		X	X	X
Emotion Regulation Questionnaire (ERQ)	Gross & John, 2003 [58]		X		X	X	X
Hopkins Symptom Checklist (SCL-10) anxiety items	Strand et al., 2009 [49]		X		X	X	X
Aggression	Roland & Idsøe, 2001 [50]		X		X	X	X
Intentions to quit school	Studsrød & Bru, 2009 [48]		X	X	X	X	X
Cognitive Competence	Harter, 1985; Paulsen et al., 2006 [46, 47]		X		X	X	X
Social Competence	Harter, 1985; Paulsen et al., 2006 [46, 47]		X		X	X	X
Social activities			X		X	X	X
Absence			X		X	X	X
Life events	Ystgaard, 1997; Murberg et al., 2004 [59, 60]		X	X	X	X	X
Satisfaction with the treatment Questionnaire	Ginsburg & Drake, 2002 [66]				X		

*S* screening, *T0* pretest Nov/Dec2015, *T1* Jan2016, *T2* June2016, *T3* Dec2016, *T4* June2017 Next cohort, *T0* Pretest Nov/Dec2016, *T1* Jan2017, *T2* June2017, *T3* Dec2017, *T4* June2018

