#### Primary outcome measures

Dropout will be measured from school reports.

The level of depressive symptoms as assessed by the Center for Epidemiologic Studies Depression Scale for adolescents (CES-D; [44]) will also serve as one of the primary study outcomes. CES-D asks for the frequency of symptoms during the last week of depressed affect (7 items), lack of positive affect (4 items), somatic and retarded activity (7 items), and interpersonal problems (2 items). A four-point Likert scale is used (total score range: 0–60). A previous confirmatory factor analysis supported the use of four dimensions invariantly to gender and differing ethnic backgrounds in Norway [45].

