#### Secondary outcome measures

A variety of secondary outcome measures will also be gathered. Social and academic functioning will be assessed by various measures. While social functioning measures include *social competence* and involvement in *social activities* with peers, academic functioning will be assessed using the measure of *cognitive competence*, and *grades* provided by the school. Perceived cognitive and social competence will be measured using slightly modified subscales from Harter’s [46] Self-perception Profile for Children [47]. In addition to *self*- *and school*-*related absence*, *intentions to quit school*, 4-item scale developed by Studsrød & Bru [48] will also be measured. *Social anxiety* will be assessed using the adapted version of the Hopkins Symptom Checklist (SCL-10) anxiety items [49]. *Reactive aggression* will be measured using an adapted version of Roland and Idsoe’s reactive aggression scale [50].

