#### Mediators

The frequency of *negative thoughts* will be assessed using the single-factor, short-form version of the Automatic Thoughts Questionnaire (ATQ; [51, 52]). It has been suggested that this short version of ATQ shows high reliability and validity, without deteriorating content domain coverage of the construct [52]. The intensity of *dysfunctional attitudes* will be measured with the revised version of the Dysfunctional Attitude Scale (DAS; [53]) which is one of the most commonly used instruments as a mediator of outcome in CBT for depression [54]. Two-factor solution with 17 items, consisting of ‘dependency’ and ‘perfectionism/performance evaluation’, demonstrated good reliability and convergent construct validity [53]. Revised version of the Ruminative Responses Scale (RRS;[55, 56]), a self-report measure of *rumination* with 10 items, will be used to measure two aspects of rumination, reflecting and brooding. This version of RRS does not include items that seem to overlap with the measures of depressive symptoms [56]. *Emotion regulation strategies* will be assessed through the Norwegian version of the Emotion Regulation Questionnaire (ERQ; [57, 58]). The ERQ is a 10-item measure that assesses the use of two common emotion regulation strategies: cognitive reappraisal and expressive suppression.

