### Sample size and power calculations

Because the design is a single-centre cluster-randomized effectiveness trial with active control, where groups rather than individuals are randomized, possible cluster effects must be accounted for when calculating appropriate sample size [61]. We approximated cluster effects influencing our main outcome (depressive symptoms) by taking advantage of data from the existent study on ACDC [37], and calculated intraclass correlations (ICC’s) with the course groups as cluster. ICC for depressive symptoms was .08. Our calculations showed that with a .05 level of significance, power = .80, ICC = .08, number of clusters = 25, cluster size = 8, *N* = 200, we may be able to detect effect sizes of .49 (about medium effects according to (Cohen, 1988). We recruited 30 course leaders rather than 25 and we can withstand a total waiver of five of the groups while still identifying the effect size we have calculated.

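### The article defines the primary outcome in three conflicting ways (seven outcomes in Table 1, two in the text, one in the power calculation), so the result that decides the trial is not fixed.

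*Protocol article*

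**What the plan says.** The protocol article assigns outcome roles in several places.

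- **Table 1, primary outcomes.** Seven entries: CES-D, DAS, ATQ, RRS, emotion regulation, dropout and grades. Examples are "2. Dysfunctional Attitudes Scale (DAS) (short version) at Pre-test, T2, T3, T4" and "7. Grades at T1, T2, T3, T4". Life events are listed there as a key secondary outcome.
- **Primary outcome measures.** Two: dropout, taken from school reports, and CES-D, which "will also serve as one of the primary study outcomes".
- **Secondary outcome measures.** Grades belong here. The sentence stating that "academic functioning will be assessed using the measure of" cognitive competence goes on to add school-provided grades.
- **Mediators.** ATQ, DAS, RRS and the Emotion Regulation Questionnaire (ERQ). DAS is described as "one of the most commonly used instruments as a mediator of outcome in CBT for depression".
- **Moderators.** Immigrant status and stressful life events.
- **Sample size and power calculations.** The authors approximated "cluster effects influencing our main outcome (depressive symptoms"), then state that "with a .05 level of significance, power = .80, ICC = .08, number of clusters = 25, cluster size = 8", giving 200 adolescents, "we may be able to detect effect sizes of .49".
- **Statistical analysis.** Repeated-measures general linear models and latent growth curve models are planned. No order of outcomes, primary contrast or significance level is given.

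**The concern.** A confirmatory trial needs one agreed answer to the question of which result decides it. Here the answer depends on where one looks. A significant effect on rumination or negative thoughts could be reported as a primary result by citing Table 1, or as a mediator result by citing the text. Grades could be primary or secondary in the same way. Table 1 is the registration data set, so the registered record and the article's own text disagree.

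The power statement is affected as well. It is worked out for one outcome and one test. If more than one primary outcome stays and the significance level is divided, the stated detectable effect no longer applies. If the level is not divided and any success counts, the chance of a false primary claim rises above 5%.

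**Working it through.** **1. Roles side by side**

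| Outcome | Table 1 | Text | Powered |
|---|---|---|---|
| CES-D | primary | primary | yes |
| Dropout | primary | primary | no |
| DAS | primary | mediator | no |
| ATQ | primary | mediator | no |
| RRS | primary | mediator | no |
| Emotion regulation | primary | mediator | no |
| Grades | primary | secondary | no |
| Life events | key secondary | moderator | no |

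That makes seven primaries in Table 1, two in the text and one in the power calculation. Five of the seven registered primaries have another role in the text (four mediators, one secondary).

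**2. Reproducing the stated .49**

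Inputs, all from the sample size section: 25 clusters of 8 (N = 200), ICC .08, level .05, power .80. Two-sided testing is an assumption, because the article does not say.

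- Design effect = 1 + (8 − 1) × .08 = 1.56.
- Standard error of the standardized difference = √(4 × 1.56 / 200) = .1766.
- Detectable effect = (1.960 + .842) × .1766 = .495.
- Power at .49 = 79.2%.

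The figure reproduces as one two-sided test of one outcome with normal critical values. A one-sided .05 test would give .439, which does not match. A t reference with 23 degrees of freedom would give .517. That difference has nothing to do with the number of outcomes, so the normal basis is kept for the comparisons below.

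**3. Error if any success counts**

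Assumptions that the article does not state: each primary is tested once at .05, and one success is enough.

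- Two independent outcomes: 1 − .95² = 9.75%.
- Seven independent outcomes: 1 − .95⁷ = 30.2%.
- Seven equally correlated outcomes, by simulation with assumed correlations: 27% at .3, 23% at .5, 18% at .7.

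Positive correlation is likely among depression, negative thoughts and rumination, so 30% is an upper value.

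**4. Detectable effect if .05 is divided equally (continuous outcome, N = 200, ICC .08)**

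| Primaries | Level each | Detectable effect | Power at .49 |
|---|---|---|---|
| 1 | .05 | .495 | 79% |
| 2 | .025 | (2.241 + .842) × .1766 = .545 | 70% |
| 7 | .00714 | (2.690 + .842) × .1766 = .624 | 53% |

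With two primaries and a t reference on 23 degrees of freedom, the detectable effect is about .58. None of these figures carries over to dropout, which is binary and for which the article gives no power calculation.

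**5. If all primaries must succeed**

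Error is then not inflated, but power falls. At an assumed 80% for each outcome and independence, it is .80² = 64% for two and .80⁷ = 21% for seven. The number of primaries and the decision rule both matter.

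**The case against.** The strongest reply is that the article does point to a lead outcome. The sample size section names depressive symptoms as the main outcome, the Design section also gives depression that standing, and the Discussion puts reducing depressive symptoms first and dropout only as a possible further benefit. This stands, and it makes the ambiguity smaller. It also supports choosing CES-D. It does not remove five extra primaries from Table 1. Nor does it settle dropout, which is in the scientific title and opens the section on primary outcome measures.

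A second reply is that multiplicity handling is commonly left to the analysis plan, which is not shown. That is right, and the absence of an adjustment rule is not the finding. An analysis plan cannot, however, make two contradictory lists both correct.

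Three stronger readings are tempting, and the document does not support them.

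- **That all seven are tested at .05.** The level .05 appears once, in the power calculation for depressive symptoms.
- **That there are 21 primary tests** (seven outcomes at T2, T3 and T4), with an error of 1 − .95²¹ = 66%. The planned repeated-measures and growth models can give one group-by-time test per outcome, and no wave-by-wave testing is stated. Seven is the fairer count.
- **That error is uncontrolled.** One can say only that this article states no control.

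It would also go too far to say that a mediator may never be tested for a treatment effect, since mediation analysis routinely does that. The fault lies in the inconsistent labels.

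**Conclusion.** The contradiction is plain and needs correction: seven, two and one primary outcomes in the same article, with life events mislabelled in a similar way. The counts rest on no assumption.

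The consequence for error is conditional. It is at most 9.75% for two outcomes and 30% for seven, with about 27% to 18% for seven at assumed correlations of .3 to .7. All of these require an any-success rule and a .05 level for each outcome, which the article does not state. The stated .49 is sound on its own normal basis, but only for a single outcome tested once at two-sided .05. This matters most now, because reconciling the lists after results have been seen by arm could not be told apart from choosing outcomes by their results.

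**What to change.** Amend Table 1 and the registry entry, with a date and a reason, before outcome data are examined by arm.

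1. Make CES-D the primary outcome, as the powered one, and name its primary contrast or time point. The sample size section names none, so this is a choice for the trial team.
2. List DAS, ATQ, RRS and ERQ as mediators, grades as secondary and life events as a moderator. Data collection stays unchanged.
3. Decide whether dropout is a key secondary or a co-primary. If it is co-primary, state the decision rule, for example Holm across the two. Under Holm, CES-D is tested at .025 in the worst case, so restate its detectable effect as about .55 on the article's normal basis (about .58 with t on 23 degrees of freedom).

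The cost is a registry update, a reworded table and fewer outcomes that can be called primary. The first cohort started in January 2016, so the change must be disclosed as made after that start.

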### Participants and recruitment

Approximately 8–12 adolescents of both genders are considered a preferred group size, and 30 groups will be recruited. The target population is students from the 1^st^ or 2^nd^ grade from upper secondary school, who are 16/17 years old. There is a maximum cut-off age of 20 years and subjects must have subclinical depression or mild to moderate depression, according to the criteria of the DSM. Inclusion will be evaluated through a semi-structured interview by the course instructor/control leader. Generally, the participants will be recruited through their general practitioner, the School Health Service, public health nurses, the Educational and Psychological Counselling Services (PPT) or the Children and Young People’s Psychiatric Out-patient Services (BUP). Exclusion criteria include presence of bipolar disorder, psychosis, substance-use, ADHD or ADD and brain damage as listed in the ACDC manual.

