### Control group: Practice-as-usual group

The participants in the control condition will not be offered any intervention, but they will receive treatment as usual. This will involve standard treatments, including no treatment or the use of pharmacotherapy, that the active control course leaders typically employ. The participants as well as the control leader will be asked about what they give/receive as usual care to examine the practice-as-usual in detail.

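### Adolescents were recruited and selected after allocation by leaders who could tell their arm, and what control leaders offered them is unclear

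*Protocol article*

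**What the plan says.** The Design section gives the order of events. Allocation comes first: "The course leaders have been randomized to experimental and control conditions by administrative personnel". Training then differs by arm: "Fifteen course leaders for the intervention group received their training for a full week in October 2015", while the 15 control leaders "received a one-day training in how to recruit adolescents in October". Enrolment follows: "Adolescents have been recruited throughout November and December 2015".

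The same section says that trainers in both arms, expressly including the control ones, do the recruiting and that "they are offering their own courses by placing information on schools and health centers". The control group section says: "The participants in the control condition will not be offered any intervention, but they will receive treatment as usual". Usual care there may include no treatment.

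The leader also decides who enters: "Inclusion will be evaluated through a semi-structured interview by the course instructor/control leader" (Participants and recruitment). Under Screening measure, written consent and the first pretest follow at that same interview. A BDI score of at least 10 is required in both arms. Some exclusions in Table 1 rest on the leader's judgement, such as "Adolescents who lack the ability to function in a group".

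**The concern.** In a cluster trial, randomisation protects the comparison of adolescents only if they are identified before allocation, or by people who cannot tell the arm. Neither is described here. A leader about to run a group, and one who will deliver only usual care, may advertise differently, receive different referrals, and apply the judgement-based criteria differently. Inability to function in a group matters in practice mainly to a leader who is going to run one.

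If the arms enrol different adolescents, later differences in CES-D and dropout mix selection with the effect of ACDC. The repeated measures GLM in the Statistical analysis section removes a stable difference in level. It does not remove a difference in the course that the adolescents would have followed anyway.

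**Working it through.** **1. Order of events (Design; Participants and recruitment; Screening measure).**

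| Step | When | Arm recognisable to the leader? |
|---|---|---|
| Leaders randomised | before the October 2015 training | – |
| Training: full week or one day | October 2015 | yes, from the training itself |
| Advertising and referral | November–December 2015 | yes |
| Interview, inclusion decision, consent, T0 | November–December 2015 | yes |

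That leaders could tell their arm is an inference, but a firm one: the training was either in running the course or only in recruiting.

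**2. The offer.** One section has both arms offering courses. Another says controls are offered no intervention. The Design section promises later ACDC training to control leaders, but states no later course for control adolescents. What control leaders offered cannot be settled from the text.

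**3. Measures before the course.** The Design section defines T1 as before ACDC starts. CES-D is taken at T0 and T1 (Table 2). Intention to quit school is also taken at T0 and T1, and absence at T0. Table 1 lists dropout and grades from T1.

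**4. The plan's own figure.** Inputs from Sample size and power calculations: 25 clusters of 8, N = 200, ICC .08, alpha .05, power .80. Two-sided testing is assumed.
- Design effect = 1 + (8 − 1) × .08 = 1.56
- SE of an arm difference in SD units = √(4 × 1.56 / 200) = .1766
- Detectable effect = (1.960 + .842) × .1766 = .495, against the stated .49. The figure is reproduced.

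**5. What a baseline comparison can show.** Assume the same ICC at baseline.
- 95% half-width = 1.96 × .1766 = .346 SD
- As a share of the target effect: .346 / .49 = 71%
- For 19 groups, if they averaged 8: SE = √(4 × 1.56 / 152) = .203, half-width .397 SD. The Study status section reports some smaller groups, which would widen this.

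**6. Illustration of the stakes.** The documents give no bias size, so the values of b are assumptions. The false-positive rate of an unadjusted two-sided 5% test is P(|Z + b/.1766| > 1.96).

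| Assumed bias b (SD) | False-positive rate |
|---|---|
| 0 | 5% |
| .1 | 9% |
| .2 | 20% |
| .3 | 40% |

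Adjustment for pre-course CES-D changes both the bias and the SE, so these rates are not predictions for an adjusted analysis.

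**7. Does a later randomisation fit the calendar?** A start on 6 February 2017 plus 14 weeks ends on 15 May 2017. Two weeks before the start is 23 January 2017. T1 stays in January and T2 in June 2017, as in the Table 2 footnote.

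**The case against.** Intake is not solely the leader's choice. Referrals come through GPs, school health services and psychiatric outpatient services, and the referrer is involved in differential diagnosis. The BDI floor is common to both arms, and study information is given before consent. With CES-D at two points before the course, a passing difference at enrolment should fade at least partly by T1, where it can be seen free of any treatment effect. The plan also allows growth models with predictors. All of this stands. It reduces the risk and makes part of it checkable. It does not balance unmeasured differences in who volunteers, is referred or is accepted.

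The article also says that recruitment procedures will be revised. The reason it gives is the shortfall in recruitment, not bias, and it does not say what will change.

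Four stronger conclusions are tempting, and the documents do not support them:
- *The offer to controls was untrue.* That depends on what adolescents were told at the interview and on whether a course followed, which the text does not show. Read literally, the recruitment sentence even means the same offer in both arms, which would lessen self-selection by arm.
- *Dropout has no measure before the course.* It is listed at T1, which precedes the course.
- *Losing 11 of 30 groups shows selection by arm.* The article blames recruitment difficulties and gives no split by arm.
- *The bias can be sized from regression to the mean between T0 and T2.* That ignores T1. With an assumed enrolment difference of .35 SD and assumed correlations of .7 (T0–T1) and .6 (T0–T2), the artefact is .35 × (1 − .6) = .14 measured from T0, but .35 × (.7 − .6) = .035 measured from T1.

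**Conclusion.** The concern holds as a design risk. Adolescents were identified, screened and consented after allocation by leaders who could tell their arm, and no arm-neutral offer is described. The size and direction of any bias are unknown, and it may be zero. What the documents do show is that a baseline table could not exclude a difference of up to about .35 SD, given ICC .08 at baseline and 25 full groups of 8. The conclusion rests on one inference, that the October training revealed the arm. It does not rest on the assumed biases in the illustration.

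**What to change.** **Cohort 2, still planned under Study status.**
- Give all leaders the same one-day recruitment training and one offer text: a study in which the group receives either ACDC or practice as usual.
- Complete the eligibility interview and T0 in November–December 2016.
- Then randomise, and hold the 5-day ACDC training in January 2017, with T1 about 23 January and the course from 6 February.
- If the training date cannot move, use the common offer text alone. Leaders would then still know their arm when they screen.

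**Analysis, both cohorts.** Estimate the CES-D effect adjusted for CES-D at T0 and T1, and show it alongside the GLM. Include cohort as a term in the pooled analysis, because the two cohorts would differ in the order of recruitment and randomisation.

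**Write-up.** State what control leaders offered in cohort 1.

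**Cost.** Leader training moves from autumn 2016 to January 2017, and the course starts some weeks later. Enrolment may be slower when the offer may lead only to usual care, in a trial where 11 of 30 groups were not established. No new measure is needed, and T2 stays in June 2017. Cohort 1 enrolment cannot be changed, so there the adjustment is only a partial remedy.
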